##### Secondary hypotheses

H4. TRE adherence will predict improvements in self-rated symptoms of mania and depression at 10 weeks and 6 months post-baseline compared to baseline symptom severity scores.H5. The degree of change in sleep and the amplitude of diurnal activity/distal temperature rhythms at week 8 will explain improvement in symptoms (week 10), controlling for baseline symptoms and sleep/diurnal rhythm amplitude.H6. The degree of change in metabolic health (CMP) at week 8 will explain improvement in symptoms (week 10), controlling for baseline symptoms and metabolic health.

To provide a more refined index of changes in emotion, we will assess the effects of TRE on daily emotional lability (as assessed using EMA, baseline and post-intervention).

We will conduct exploratory analyses to examine secondary outcomes (e.g., EMA) and potential moderators.

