### Circadian and sleep disruption in bipolar disorder (BD)

Considerable evidence supports a strong association between biological rhythm disturbances and the pathogenesis of BD [34]. Disturbed sleep-activity rhythms are principal symptoms observed in manic and depressive episodes [35, 36], and these disturbances continue at lower levels for most people with BD during remission [37–40]. Sleep disturbances predict both BD onset and symptom increases in naturalistic studies of sleep, jet lag, activity, and sleep deprivation [40–45]. These issues predict vulnerability to the disorder, with evidence linking (a) BD to single-nucleotide polymorphisms within multiple clock genes, (b) mood variability to polygenic risk scores related to chronotype and low circadian amplitude, and (c) disruptions in sleep/sleep-activity rhythms [46–48] in family members of those diagnosed with BD. Accordingly, there is a need for interventions that target the circadian timing system to stabilize biological rhythms in patients with BD.

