#### Primary outcomes

Our primary outcome measures will be: interview-based assessments of mood symptoms, and a brief self-report measure of Quality of Life, which were chosen based on strong psychometric characteristics, including high interrater reliability for the interview-based measures. Where possible, the symptom severity interviews will be conducted by raters who are unaware of the participant’s intervention status (which is feasible as our team is conducting a parallel study involving the Mediterranean diet). Where a rater becomes inadvertently aware of the intervention status, we will attempt to replace the interviewer for that participant.

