##### Montgomery-Asberg Depression Rating Scale (MADRS; [114])

The MADRS is a brief measure designed to assess the severity of depressive symptoms.

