##### Young Mania Rating Scale (YMRS; [87])

The YMRS is an 11-item interview designed to assess the severity of manic symptoms.

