##### Sleep and diurnal rhythm assessment via actigraphy and distal temperature

We will use the GENEActiv (Activinsights Inc.) wristband to record continuous activity counts and ambient light-exposure. Actigraphy data will be collected during baseline for two weeks and for 3 weeks at week 7. An integrated RGB light sensor records light measurements to help assess the impact of ambient light on human circadian and sleep physiology. The GENEActiv wristband is capable of a month of continuous recording and will not need to be recharged during the period of wear. The device is waterproof, allowing participants more freedom to wear the watch when completing normal activities. Actigraphy data are collected via an onboard 3-axis accelerometer and will be analyzed for sleep onset, offset, duration, and efficiency. Diurnal rhythm amplitude and stability will also be assessed using this activity data. Participants will be provided instructions and will not have access to data as it is collected on the device. Clocklab software (Actimetrics, Lafayette IN) will be used to calculate diurnal amplitude, mesor, and acrophase. Interdaily stability (IS), and intradaily variability (IV) will be calculated using non-parametric analyses in Clocklab. Sleep onset, offset, duration, and efficiency indices will be determined using validated algorithms from Activinights.

As a secondary measure of diurnal rhythmicity, we will use iButtons to record wrist temperature (temperature logged every 5 min). The iButton is a small (17.35 mm diameter × 5.89 mm depth) data logger that can be used to record human skin temperature at selected intervals and is regularly applied to studies of circadian rhythms and sleep/wake research (e.g., [123, 124]). iButtons will be used to chronically record wrist skin temperature when actigraphy measures are collected. The iButtons will be placed on the top of the wrist and secured in place with self-adherent cohesive wrap tape made of medical-grade non-woven, hypoallergenic fabric.

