To supplement our primary indices of circadian function, we will examine changes in sleep (the gold standard CORE CSD measures of quality of sleep and reduced variability in sleep midpoint, along with PROMIS sleep disturbance and sleep-related impairment, and actigraphy and temperature measures). To assess whether the sleep and light guidance offered as part of the TRE intervention leads to improved sleep hygiene, we will gather the Sleep Household Environment and In-Bed Behaviors [92].

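### If the symptom scores used for H5 include a sleep item, part of the H5 association is sleep predicting sleep, and the baseline adjustment does not remove it

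*Protocol article*

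**What the plan says.** Under Secondary hypotheses, H5 reads "The degree of change in sleep and the amplitude of diurnal activity/distal temperature rhythms at week 8 will explain improvement in symptoms (week 10", with the adjustment given as "controlling for baseline symptoms and sleep/diurnal rhythm amplitude". H5 names neither a symptom scale nor a score.

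The primary symptom measures are "interview-based assessments of mood symptoms" (Primary outcomes). Of the two scales, the article says "The MADRS is a brief measure designed to assess the severity of depressive symptoms" and "The YMRS is an 11-item interview designed to assess the severity of manic symptoms". Two self-report scales, the PHQ-9 and PMQ-9, are secondary outcomes. No item content is given for any of the four.

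The background section on circadian and sleep disruption in BD says: "Disturbed sleep-activity rhythms are principal symptoms observed in manic and depressive episodes".

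The sleep measures are the sleep diary, "along with PROMIS sleep disturbance and sleep-related impairment, and actigraphy and temperature measures". On timing: "Actigraphy data will be collected during baseline for two weeks and for 3 weeks at week 7".

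The Statistical analysis plan section keeps variables entangled with sleep and circadian processes out of the covariate set. It has no matching rule for the outcome score.

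**The concern.** By the article's own account, sleep disturbance is part of what mania and depression severity consist of. H5 puts change in sleep on the predictor side and mood-symptom severity on the outcome side. If the severity score includes a sleep rating, the same improvement in sleep is counted on both sides.

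The stated controls do not separate the two. Baseline symptoms and baseline sleep/rhythm amplitude fix the starting point, but a later change in sleep still moves both the week-8 predictor and any sleep content of the week-10 score. The nominal gap between week 8 and week 10 helps little, because the actigraphy window of three weeks from week 7 runs up to about the week-10 rating.

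What is at stake is interpretation. The study has a single arm and its stated aim is mechanism, so conclusions rest on associations of this kind. A significant H5 would be read as better sleep relieving depression or mania when it might show only that better sleep lowers a sleep item.

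**Working it through.** **Plan figures.** The article gives no effect size or power for H5; its stated power of .81 is for the indirect effect of clock-gene amplitude, so there is no H5 figure to reproduce. The usable inputs are n = 125 (150 recruited less 25 for attrition), two-sided alpha of .05, two covariates (the number assumed in the article's power analysis) and 11 items for the YMRS.

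**Assumptions not in the documents.**
- The score has m = 10 or 11 items of equal variance, and exactly one rates sleep.
- The sleep measure correlates v = .3, .5 or .7 with that item, read as a correlation after the baseline adjustment.
- Sleep change has no link with the other items.
- The other items correlate with each other at ρ = 0 to .3, and not with the sleep item.

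**Step 1: share of the sleep item in the total.** With unit item variances, the variance of the total is 1 + (m − 1) + (m − 1)(m − 2)ρ, so

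corr(sleep item, total) = 1 / √[m + (m − 1)(m − 2)ρ].

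- m = 10: 1/√10 = .316 at ρ = 0; 1/√(10 + 72 × .3) = 1/√31.6 = .178 at ρ = .3.
- m = 11: 1/√11 = .302 at ρ = 0; 1/√(11 + 90 × .3) = 1/√38 = .162 at ρ = .3.

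**Step 2: induced correlation.** r = v × the factor from step 1.

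**Step 3: chance of significance.** By Fisher's z, the mean of the test statistic is atanh(r) × √(125 − 2 − 3) = atanh(r) × 10.95. The rejection probability is Φ(mean − 1.96) + Φ(−mean − 1.96). Example with m = 10, v = .7, ρ = 0: r = .221, atanh(r) = .225, mean = 2.47, probability = 69%.

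| m | v | r (ρ = .3 to 0) | Chance of p < .05 (ρ = .3 to 0) |
|---|---|---|---|
| 10 | .3 | .05 to .09 | 9% to 18% |
| 10 | .5 | .09 to .16 | 16% to 42% |
| 10 | .7 | .12 to .22 | 28% to 69% |
| 11 | .3 | .05 to .09 | 8% to 17% |
| 11 | .5 | .08 to .15 | 14% to 38% |
| 11 | .7 | .11 to .21 | 24% to 65% |

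**Step 4: effect size.** f² = r²/(1 − r²). The largest value is .049/.951 = .05, against the .25 that the article calls moderate (for amplitude on symptoms and QoL).

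**Step 5: sensitivity to one assumption.** Let the sleep item also correlate .3 with the other items, still with no link between sleep change and those items. The factor for m = 10 becomes 1/√(10 + 90 × .3) = 1/√37 = .164. The chance of significance is then 8%, 15% and 24% for v = .3, .5 and .7, slightly below the ρ = .3 figures in the table.

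**Step 6: after removing the sleep item.** In this scenario the induced correlation is 0 and the rejection rate returns to 5%.

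**The case against.** The strongest reply is that the overlap is not in the document. No scale items are listed, and a principal symptom of an episode need not be an item on a severity scale. A reader might infer that the totals are shown to rate sleep and that H5 regresses those totals on sleep. The article supports neither: H5 says only symptoms, and the choice of score may be settled in an analysis plan that is not shown. This stands, and it makes the point conditional. It does not dispose of it, because the article's own description makes a sleep item likely enough to check, and its only entanglement rule concerns covariates.

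Second, if sleep disturbance is a symptom, a fall in a sleep item is real symptom improvement, so a significant H5 is not false as worded. This also stands. The 8% to 69% is the chance of a significant result when no other mood symptom is related to sleep change; it is not a type I error rate for H5 as worded.

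Third, the size rests on assumed inputs. The 69% needs v = .7 and no correlation among the other items, which is implausible within one symptom scale; with ρ = .3 the highest figure is 28%. The induced effect is small throughout.

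Fourth, the reach is limited. H5 is secondary. The overlap bears most directly on diary, PROMIS and actigraphic sleep, and less on activity and temperature amplitude. A reader might extend the point to the lagged tests of sleep and mood described under Hypotheses. The article gives their outcome as EMA Mood Zoom variability, not a symptom-scale total, so the extension fails.

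**Conclusion.** The concern holds in conditional form. If the score used for H5 contains a sleep item, part of the association is sleep predicting sleep, and neither the baseline adjustment nor the two-week lag removes it. Under the stated assumptions the induced correlation is about .05 to .22 (f² at most about .05) and the chance of a significant H5 at n = 125 is about 8% to 69%, against 5%. The effect is too small to pass for the moderate effect the article has in mind, but large enough to reach significance and be read as a mechanism.

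The item content, the correlation of the sleep measure with the item, the equal variances and the inter-item correlations are assumptions. The documents do not show that the scales rate sleep or that unmodified totals will be used. H1 to H3 take no sleep rating as predictor and are untouched.

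**What to change.** First check on the case report form whether the symptom score or scores used for H5 contain a sleep item. If so, for H5 only:

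- pre-specify a parallel analysis with the sleep items removed from those scores, at baseline and at week 10;
- report it beside the analysis of the full scores;
- claim that sleep improvement explains improvement in other mood symptoms only if the sleep-free result holds.

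Leave the lagged EMA tests and H1 to H3 as they are.

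The cost is a sentence in the analysis plan and a re-scoring, with no new data provided item-level scores are stored. The downside is that the shortened scores are not comparable with published cut-offs, which is a reason to keep the full scores in the report.

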## Methods

This trial will be conducted by an international multidisciplinary team of researchers, clinicians, and lived experience experts. The study was reviewed and approved by the University of California Committee for the Protection of Human Subjects (protocol number CPHS # 2022–10–15725). The trial objectives and protocol align with all aspects of the WHO Trial Registration Data Set (version 1.3.1) and the Standard Protocol Items: Recommendations for Interventional Trials guidelines [75]. We will describe any changes to this trial protocol in publications. We will report scientific findings according to the Consolidated Standards of Reporting Trials (CONSORT) general guidelines and the eHEALTH criteria [76]. Potential financial conflicts of interest will be reviewed annually by the University of California committee for conflicts of interest, and their guidance will be followed in managing any conflicts identified.

### Trial design

The trial is a non-randomized, single arm (TRE) study. The primary endpoint is immediately after the 8-week-long TRE period (end of week 10). The follow-up assessments will be conducted at 6 months after the baseline, supplemented with post-baseline self-reported assessment at week 16. Hypothesized mechanisms of change will be tested at baseline and at 8 weeks post-baseline. The study setting is remote (online food plan materials, questionnaires, and interviews), supplemented with at-home collection of biological data (DLMO, clock genes, actigraphy, CGM) and assays completed by Quest Diagnostics (CMP, glucose tolerance test).

### Inclusion/exclusion criteria

The inclusion/exclusion criteria are designed to maximize participant safety and the applicability of TRE, and secondarily, to maximize the generalizability of the findings. We will recruit adults aged 18–65 years who meet diagnostic criteria for bipolar I disorder or bipolar II disorder per the Diagnostic Interview for Anxiety, Mood, and OCD and Related Neuropsychiatric Disorders (DIAMOND), but not cyclothymia, BD not otherwise specified, or BD due to another medical condition.

To maximize the ability to determine whether TRE improves sleep- or circadian-related outcomes, the entrance criteria will include at least some current sleep or circadian sleep–wake concerns. We do not expect this to greatly diminish generalizability, as more than 75% of those with BD report sleep or circadian concerns [77]. This inclusion criteria will be met by any one of the following:

Score of ≥ 8 reflective of subsyndromal insomnia on the Insomnia Severity Index (ISI; [78–80])Early chronotype (midpoint of sleep on free days < 4.16 h) or late chronotype (midpoint of sleep on free days > 4.53) on the MCTQDisrupted social activity rhythms, as indicated by a score ≥ 30 on the Brief Social Rhythm Scale (BSRS) [81]Sleep (insomnia, hypersomnolence) or circadian sleep–wake (delayed phase, advanced phase, irregular sleep–wake, non-24-h sleep–wake-type) disorder diagnoses on the Structured Clinical Interview for Sleep Disorders-Revised (SCISD-R; [82]).

Other inclusion criteria include the following:English language adequate for completion of questionnaires or interviews, as indicated by speaking English for at least 10 years, speaking English at home, or proficiency as observed during the screening interview.Receiving medical care for BD (referrals will be provided for those who would like to begin care)Mood-stabilizing medication regimens need to be stable for at least one month. Those with BD II per the DIAMOND will be permitted to engage in the trial if not taking mood-stabilizing medication, as long as their provider has supported this treatment plan and continues to see them at least once every 3 months.Currently eating ≥ 12 h per day at least twice per weekAble to operate the camera function and respond to surveys by smartphone (loaner phones will be provided as needed)

Exclusion criteria include the following:Current episode of depression, hypomania or mania, or psychosis (per the DIAMOND).Suicidal ideation coupled with current plan or intent or history of attempt as assessed by the Columbia Suicide Severity Rating Scale (C-SSRS).Eating disorder diagnosis (self-reported history of treatment or diagnosis, Short Eating Disorder Examination Questionnaire (EDE-QS; [83]) scores above clinical concern thresholds for eating disorders (≥ 15) or DIAMOND diagnosis of eating disorder (anorexia, bulimia, binge eating disorder or other specified eating or feeding disorders).Past 3-month alcohol use disorder or substance use disorder (per the DIAMOND)Current shift work or responsibilities, such as providing care, that would chronically disrupt sleep (i.e., > 3 h between 22:00 and 05:00 h for at least 1 day/week) > 5 kg weight change in the past 3 monthsConditions that would interfere with ability to take part in TRE, including type I diabetes, pregnancy, breastfeeding, uncorrected hypo- or hyperthyroidism, or gastrointestinal conditions impairing nutrient absorption.Medical conditions that could confound immune or other study measures, such as HIV, AIDS, multiple sclerosis or lupusMedications contraindicated for fasting; clozapine; glucose-lowering medications; diabetes or obesity-related injections; medications requiring food early in the morning or late in the evening, corticosteroids; GLP-1 agonists (such as Semaglutide) will not be an exclusion criteria if weight is stabilizedCognitive deficits as noted during the initial interview or as indicated by low performance on the Brief version of the Orientation Memory Concentration Test (Weighted, reverse score < 20)Failure to complete screening and baseline questionnaires adequately (see strategies to maximize data quality procedures below).Failure to complete 7 days of dietary logs adequately (e.g., at least 2 entries per day, covering at least a 5-h eating window) during the baseline period.

### Recruitment and assessment

Recruitment and screening procedures will be parallel with those reported previously [69]. Briefly, participants will be recruited from community and clinic centers, and we will advertise to oversample those in the early stage of their illness (within 5 years of onset). Screening will begin with completion of online informed consent, and then an online screening survey to assess medical and demographic criteria, and to complete self-rated psychiatric screeners for eating disorder symptoms, alcohol, substance and psychosis symptoms. Those who meet criteria within the screening survey will be scheduled for a remote interview consisting of the DIAMOND interview to assess psychiatric diagnoses, and the Structured Clinical Interview for Sleep Disorders-Revised (SCISD-R) [82] to assess sleep disorders (insomnia, hypersomnolence disorder) and circadian sleep–wake disorders (irregular sleep–wake disorder and non-24-h sleep–wake type disorder). Participants will be paid $25 USD per hour for baseline and follow-up assessments but not be paid for other components of the study (screening, coaching and time spent implementing the dietary plan).

#### Screening interview

Participants who do not have a medical provider for their BD or who are experiencing acute mood episodes or suicidality will be provided with support and referral information and invited to recontact us once treatment and symptom stability are in place, with follow-up planned. Similarly, those who are not weight stable will be invited to recontact us once their weight stabilizes.

#### Baseline assessment

Participants who meet the eligibility criteria will be asked to complete a two-week baseline. The baseline assessments will include daily food logs, sleep diaries, and EMA probes sent via smartphone app notifications, interview measures, self-report questionnaires, actigraphy, and biological measures.

##### Food logs

Throughout the baseline period, participants will be asked to complete daily online food logs to monitor food intake and timing. The logs are designed to be simple to use and to lower burden by allowing participants to take a photo of their food or to briefly note the food without the burdens of inputting portion size or calories. Participants can complete their diet log in real time, although missed entries can be added retroactively. The validity of this daily logging approach is well-validated [84].

Continuing with the study will be contingent on adequate completion of food logs for at least 7 days during the baseline period. Adequate logging on a given day will be defined as entry of at minimum two logs at least five hours apart.

Strategies to foster logging adherence are detailed elsewhere [69]. At the end of the first week, participants with no days of adequate logging will be excluded from the study (unless we identify a barrier that can be addressed). After 10 days, those who have completed less than 50% of their assigned logs will be reminded that study continuation will depend on successful logging and given an opportunity to receive support around barriers to logging; if warranted (e.g., the patient experienced technical or travel barriers), we will extend the baseline period for four additional days.

##### EMA assessments

*Optional.* Starting on day 5 of the baseline period, for individuals who have opted into the EMA portion of the study, we will send probes by app to gather sleep and affect measures. Participants will be asked to complete the Core Consensus Sleep Diary (Core CSD) [85] each morning for 10 days. They will also be asked to complete 5 EMA prompts per day for 7 days to assess mood fluctuations (detailed below). We will send the Core CSD and EMA probes on at least 2 free days for each person (e.g., one Saturday and Sunday).

##### Interview and self-report assessments

After at least 3 days of adequate logging, participants will be sent links to schedule the baseline interview; Montgomery-Asberg Depression Rating Scale [MADRS]) [86]; Young Mania Rating Scale [YMRS]; [87]; and to complete baseline questionnaires. Baseline questionnaires will include demographic information, symptoms, sleep, and functional information (Patient Mania Questionnaire [PMQ-9]; [88]), Patient Health Questionnaire [PHQ-9]; [89], and Brief Quality of Life in Bipolar Disorder (QoL.BD; [90]), PROMIS Sleep Disturbance and Sleep-Related Impairment [91], Sleep Household Environment and In-Bed Behaviors [92], and World Health Organization Disability Assessment Schedule (WHODAS 2.0-Brief; [93]). The participants will also be asked to complete measures of potential moderators (Household Food Security Survey [HFSSM]; [94]), Positive Urgency [95], and for women in appropriate age ranges, the Menopause-Specific QoL Sleep [hot-flash] items [96, 97]).

